### Statistical analysis

Statistical analysis will be conducted at the Center for Evidence-Based Medicine of Beijing University of Chinese Medicine using Statistic Package for Social Science (SPSS, version 22.0, Beijing University of Chinese Medicine). Intention-to-treat and per protocol sets will be used to analyze the efficacy of TCHM. A safety analysis set will be used to evaluate the safety of the trial. Missing outcome variables will be estimated using the principle of the last observation carried forward, with the data from the last study follow-up used as the final results.

The independent-samples *t* test or Mann-Whitney test will be used for comparison of the trial primary outcomes between the two groups, including UAER in the early stage subgroup, 24-h UP in the middle-stage subgroup, and eGFR in the advanced-stage subgroup, which are all continuous variables with four measurements. Moreover, repeated measures analysis of variance will be attempted to further test the time effect and treatment cross-effect. With regard to the secondary outcomes, the independent-samples *t* test or Mann-Whitney test will be used to analyze continuous variables, and the chi-squared test will be used to analyze classified variables. With regard to safety outcomes, the incidence of AEs will be determined and a comparison between the two groups will be attempted. A stratified analysis of data according to DKD stage or center will be attempted in order to decrease bias. A *P* value < 0.05 will be considered to indicate a statistically significant difference.

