## Methods/design

### Study design

The proposed study is a prospective, multicenter, assessor- and analyst-blinded, pragmatic randomized controlled trial. A total of 266 participants will be recruited at the following six tertiary A hospitals of TCM in Beijing: Dongzhimen Hospital Affiliated to Beijing University of Chinese Medicine, Guang’anmen Hospital, China Academy of Chinese Medical Sciences, Beijing Hospital of Traditional Chinese Medicine, Wangjing Hospital, China Academy of Chinese Medical Sciences, Xiyuan Hospital, China Academy of Chinese Medical Sciences, Beijing Hospital of Integrated Traditional Chinese and Western Medicine, and Fangshan Traditional Medical Hospital of Beijing. Eligible patients who agree to participate will be randomly allocated at a 1:1 ratio to either the experimental group or the control group according to disease stage. After randomization, patients in the experimental group will receive basic treatment and TCHM, whereas patients in the control group will receive basic treatment only. The treatment will continue for 24weeks in both groups. Four visits will be scheduled for each patient: weeks 0 (baseline), 4, 12, and 24. The study flowchart is shown in Fig. 1. The Standard Protocol Items: Recommendations for Interventional Trials (SPIRIT) Checklist is presented in Additional file 1.

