### Data collection

A standardized CRF designed for this study will be used to collect relevant data. The participants will be evaluated at baseline and weeks 4, 12, and 24. Each visit will have to occur within 5 days from the scheduled time. Information about the participants, including demographics, medical history, and previous medications, will be collected at baseline. Data on symptoms and TCM syndrome and results of physical examination and laboratory tests will be collected at each visit; HbA1c will be measured at baseline and at weeks 12 and 24. SF-36 will be administered only at the first and last visits. The schedule of the trial can be found in Fig. 2.

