### Sample size

To estimate the group size, a small-scale study was conducted to measure the effects of TCHM in 90 patients, with 30 patients with DKD of each stage. Half of the patients regularly received herbal therapy, while the other half received basic treatment only. After 24 weeks, UAER in the control and experimental groups (early stage DKD) was70 ± 51 mg and 44 ± 27 mg, respectively, 24-h UP in the control and experimental groups (middle-stage DKD) was 3.25 ± 1.09 and 2.50 ± 0.95 g, respectively, and eGFR in the control and experimental groups (advanced-stage DKD) was 33.4 ± 9.1 and 40.5 ± 10.2 mL/min/1.73m^2^, respectively. Using early stage DKD as an example, the following formula was employed to calculate the sample size that would allow obtaining a significantly lower UAER in the experiment group after 24 weeks of treatment:$$ n={\left({\mu}_{\upalpha}+{\mu}_{\upbeta}\right)}^2\times \left(1+1/\mathrm{k}\right)\times {\sigma}^2/{\left({\mu}_2-{\mu}_1\right)}^2, $$

where *σ*^2^is overall variance, which was estimated as sample variance s^2^:$$ {s}^2=\left({s_1}^2+\mathrm{k}{s_2}^2\right)/\left(1+\mathrm{k}\right). $$

The proportion of cases between the experimental and control groups was set to 1:1(k = 1). The study was designed to have a power of approximately 90% and a one-side level of significance of 0.05 (*α* = 0.05, *β* = 0.1). *μ*_1_, *μ*_2_, *s*1, and *s*_2_ are mean and standard deviations in the control and experimental groups. This resulted in *n* = (1.64 + 1.28)^2^ × (51^2^ + 27^2^/(70 − 44)^2^ = 42.

Thus, after assuming a dropout rate of 20%, the sample size for the early stage subgroup in each group was determined to be 53. Similar calculations resulted in a sample size of 40 patients for the middle-stage and advanced-stage subgroups in each group. This produced the final sample size of 266 patients.

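### Last observation carried forward is the only stated rule for missing outcomes, so the final comparison mixes earlier-visit values with week-24 values and can be biased in either direction

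*Protocol article*

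**What the plan says.** The Statistical analysis section of the protocol article fixes one rule: "Missing outcome variables will be estimated using the principle of the last observation carried forward". The same sentence goes on to name the value that enters the analysis for a participant whose outcome is missing: "with the data from the last study follow-up used as the final results". The rule is not limited to any endpoint, and no sensitivity analysis of it is stated. On populations the section says "Intention-to-treat and per protocol sets will be used to analyze the efficacy of TCHM", and on the primary test "The independent-samples *t* test or Mann-Whitney test will be used for comparison of the trial primary outcomes between the two groups".

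Other sections decide how the rule will work in practice:

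- Study design: "Four visits will be scheduled for each patient: weeks 0 (baseline), 4, 12, and 24".
- Data collection: "SF-36 will be administered only at the first and last visits", and "HbA1c will be measured at baseline and at weeks 12 and 24".
- Sample size: the group sizes were set "after assuming a dropout rate of 20" per cent.
- Handling of withdrawal and dropout: a participant may be removed for, among other reasons, a creatinine rise of more than half over baseline, end-stage renal disease, severe complications or a serious adverse event.
- Randomization and blinding: patients, investigators and therapists know the allocation. The Discussion accepts that participants given the arm they did not want may comply poorly.

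**The concern.** A participant who leaves early enters the final comparison with a value from week 0, 4 or 12, and the t test or Mann-Whitney test treats it as a week-24 result. At the planned dropout this applies to about 8 of 40 values per arm in the middle and advanced stages (0.2 × 40) and about 11 of 53 in the early stage (0.2 × 53 = 10.6).

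Two features of this trial make that more than a formality. First, removal for renal deterioration is allowed, so a participant may be analysed on a value taken before the deterioration that caused the removal. Second, knowledge of the allocation can produce different dropout in the two arms. If eGFR is falling, the arm that loses more patients keeps more of its earlier, higher values and looks better for that reason alone. The per protocol set does not test the carry-forward assumption.

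**Working it through.** **1. The plan's own figures.** Inputs are from Sample size: one-sided α 0.05, power 90%, 1:1 allocation, and the pilot means and SDs. The formula is n = (1.64 + 1.28)² × (s₁² + s₂²) / difference².

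| Stage | Difference | SDs | n per arm | n / 0.8 | Stated |
|---|---|---|---|---|---|
| Early (UAER) | 26 | 51, 27 | 42.0 | 52.5 | 53 |
| Middle (24-h UP) | 0.75 | 1.09, 0.95 | 31.7 → 32 | 40 | 40 |
| Advanced (eGFR) | 7.1 | 9.1, 10.2 | 31.6 → 32 | 40 | 40 |

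The total is 2 × (53 + 40 + 40) = 266. The plan reproduces.

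**2. Power under carry-forward.** If 20% of values carry a fraction f of the effect, the expected difference is (0.8 + 0.2f) times the planned one, on 53/40/40 per arm. Power is from the noncentral t distribution with pooled SD √((s₁² + s₂²)/2). The three stages agree to within one percentage point.

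| Case | Per arm | Effect retained | One-sided | Two-sided |
|---|---|---|---|---|
| Planned completers | 42/32/32 | 100% | about 90% | about 82% |
| Carried values show no effect (f = 0) | 53/40/40 | 80% | about 83% | about 74% |
| Carried values show half the effect (f = 0.5) | 53/40/40 | 90% | about 90% | about 83% |

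The half-effect case breaks even because the larger sample offsets the dilution: 0.9 × √(40/32) = 1.006.

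**3. Bias in a mean (advanced stage).** Assumptions not in the documents: control eGFR falls 7 mL/min/1.73m² linearly over 24 weeks, the experimental arm is stable, and control dropouts have their last visit at week 4 or week 12 in equal numbers. The share of the decline missed is 0.5 × 20/24 + 0.5 × 12/24 = 0.667.

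- 20% control dropout: 0.20 × 7 × 0.667 = 0.93, which is 13% of the planned 7.1.
- 30% control dropout: 0.30 × 7 × 0.667 = 1.40, which is 20% of 7.1.

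The control mean is overstated, so the treatment difference shrinks.

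**4. Direction.** A simulation (4000 runs, 40 per arm, two-sided test) used further assumptions not in the documents: baseline eGFR 42, linear change, SD 9.65, within-patient correlation 0.8, last visit equally likely at week 0, 4 or 12, and dropout unrelated to outcome within arm. The mean share of change missed is 1 − (0 + 4/24 + 12/24)/3 = 0.778.

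- True difference 7.1, 20% dropout in both arms: expected 7.1 × (1 − 0.2 × 0.778) = 6.0; simulated 6.04, power 78%.
- No true effect, both arms falling to 36, dropout 10% control and 30% experimental: expected (0.30 − 0.10) × 6 × 0.778 = 0.93 in favour of the experimental arm; simulated 0.97, type I error 7.3%.
- No true effect, both arms falling to 33.4, dropout 5% control and 35% experimental: expected 0.30 × 8.6 × 0.778 = 2.0; simulated 2.06, type I error 14.2%.
- No true effect, 20% dropout in both arms: type I error about 5%.

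**5. SF-36.** With only a first and a last assessment, baseline is the only value available for a missing week-24 score. With 20% dropout in both arms, unrelated to outcome, any effect on the week-24 score shrinks to 80% of its size. HbA1c has a milder form of this, since only week 0 or week 12 can be carried forward.

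**The case against.** Several parts of the defence stand.

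- **Power.** A reader might set the two-sided 74% against the planned 90%. The planned 90% is one-sided, so that comparison charges carry-forward with a change of sidedness. Like for like the loss is 7 to 9 points, it needs every carried value to show no effect although visits take place at weeks 4 and 12, and it disappears in the half-effect case.
- **Standard errors.** A reader might infer that standard errors will simply be too small. With 20% dropout in both arms and a true difference, the average standard error (2.19) matched the spread of the carry-forward estimate (2.20). The test is arithmetically sound for what it estimates. The understatement exists only relative to the true week-24 effect: counting 40 values where 32 were observed gives √(32/40) = 0.89 of the observed-data standard error.
- **Dropout inflation.** Dividing by 0.8 is not an error. It suits the per protocol set, and it also preserves intention-to-treat power if carried values hold half the effect.
- **The eGFR example.** The decline is assumed, and the resulting bias is towards no difference. The documents give no 24-week course for UAER or 24-h urinary protein under basic treatment, so the argument from a worsening outcome is illustrated for one of the three primary outcomes only.
- **SF-36.** It is a secondary outcome, and the wording about the last follow-up could be read as excluding week 0. In that case the stated rule supplies no value at all for a missing SF-36 score.

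None of this supports carry-forward as the sole method. The rule is fixed in the text rather than left to a later analysis plan, and under unequal dropout it is not reliably conservative.

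**Conclusion.** The point holds as a concern about which quantity is estimated and about possible bias. It does not show a demonstrated loss of power or a faulty standard error. Neither direction nor size can be fixed from the documents: similar dropout dilutes a real effect, while unequal dropout with a worsening outcome favours the arm that loses more patients. Under the assumptions above, the power cost runs from none to 7–9 points. The eGFR distortion runs from a shrinkage of 0.9 to 1.4 mL/min/1.73m² to a spurious gain of about 1 to 2. These are illustrations, not predictions. The SF-36 consequence needs no assumption about trajectories, only that baseline counts as an observation that can be carried forward.

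**What to change.** Replace carry-forward as the primary method. In each stage, analyse the primary outcome with a baseline-adjusted mixed model for repeated measures on all observed visits, and report the week-24 contrast between arms as the result. This can also take the place of the repeated measures analysis of variance that the plan says will only be attempted. For SF-36, use a baseline-adjusted analysis with multiple imputation. Keep carry-forward as a sensitivity analysis, and add one aimed at outcome-related withdrawal, for example a delta-adjusted analysis. Detailed model specification can be left to the analysis plan.

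The cost is wording plus standard procedures; visits, participants and sample size do not change. The article reports that recruitment is under way, so the change can be made before the data are analysed. The downside is that the primary analysis then relies on data being missing at random, which the withdrawal sensitivity analysis is there to probe.

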**Methods/design:**

This will be a multicenter randomized controlled trial. A total of 266 patients with DKD (106 with early stage, 80 with middle-stage, and 80 with advanced-stage disease) with an estimated glomerular filtration rate (eGFR) ≥ 30 mL/min/1.73m^2^will be included. Participants with DKD of each stage will be randomly allocated at a 1:1 ratio to either the experimental group, which will receive *Xiaozhen* formula and basic treatment, or the control group, which will receive basic treatment only. The study duration will be 24 weeks. The primary outcome will be urinary microalbumin excretion rate for early stage DKD, 24-h urinary protein for middle-stage DKD, and eGFR for advanced-stage DKD. Adverse events will also be evaluated. Data for all outcome indicators will be collected at baseline and weeks 4, 12, and 24.

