### Randomization and blinding

The random sequence will be generated by the Center for Evidence-Based Medicine of Beijing University of Chinese Medicine using Statistical Analysis System (SAS version 9.2), and randomization will be stratified according to study center and DKD stage. Eligible patients with DKD of each stage will be randomized to the experimental group or the control group at a 1:1 ratio. The group numbers will be provided in envelopes made from carbonless paper. At each center, the envelopes will be kept by a study administrator who will not directly participate in the recruitment or follow-up of any participant, and the group numbers will be subsequently disclosed. The administrator will open one envelope and provide the participant with their group number on the day of inclusion.

Different people will serve as investigators, therapists, and assessors. Assessors of primary and secondary endpoints and data analysts will be blinded to the treatment allocation throughout the course of the study, while patients, investigators, and therapists administering the treatment will not be blinded.

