#### Laboratory tests

Routine laboratory tests (CBC and general urine analysis, Scr, BUN, AST, ALT, ALP, GGT, UAER, 24-h UP, and HbA1c) will be performed by the clinical laboratory of each center. For CRP, IL-6, and TNF-a level determination, an additional 3–5 mL of venous blood will be collected. The serum will be separated by centrifugation for 15 min at 3000×g, aliquoted, labeled concisely, and stored at − 80 °C until the final analysis. Repeated freeze-thaw cycles will be avoided. The inflammation indicators will be measured at the Research Center, Dongzhimen Hospital Affiliated to Beijing University of Chinese Medicine using specific ELISA kits.

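### The primary test in each stage leaves out the collected baseline value and makes centre optional: a valid choice, but one that forgoes precision

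*Protocol article*

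**What the plan says.** For the primary outcomes (UAER in early, 24-h UP in middle and eGFR in advanced stage), the Statistical analysis section states that the independent-samples t "test or Mann-Whitney test will be used for comparison of the trial primary outcomes between the two groups". It describes these outcomes as variables "which are all continuous variables with four measurements". No covariate is named.

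Two further analyses are mentioned, both tentatively: "repeated measures analysis of variance will be attempted to further test the time effect and treatment cross-effect", and "A stratified analysis of data according to DKD stage or center will be attempted in order to decrease bias". Neither is put forward as the primary test.

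The baseline value is available. The abstract states: "Data for all outcome indicators will be collected at baseline and weeks 4, 12, and 24". The legend of Fig. 2 can be read as giving fewer visits for 24-h UP, but week 0 is included on either reading.

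Under Randomization and blinding, "randomization will be stratified according to study center and DKD stage". Under Laboratory tests, the routine assays, including UAER, 24-h UP and the serum creatinine behind eGFR, "will be performed by the clinical laboratory of each center". The Discussion acknowledges that the centres may differ in their experience with the treatment.

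**The concern.** The baseline value of the same variable is usually the strongest predictor of a week-24 laboratory value. Patients enter over wide ranges: the Stage differentiation section allows UAER of 30–300 mg/24 h in early stage and eGFR of 30–60 mL/min/1.73 m² in advanced stage. With a few dozen patients per arm in each stage, the arms can differ at baseline by chance, and an unadjusted comparison at week 24 carries part of that difference into the estimate.

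Centre raises a second, smaller issue. Stratified randomization balances the arms within centres. If centres differ in outcome level, for example through their laboratories, a test that ignores centre leaves that variation in the error term, and its standard error is too wide.

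At stake are the width of the confidence interval and the credibility of the estimate if the arms happen to differ at baseline. The validity of the test is not at stake.

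**Working it through.** **Inputs from the Sample size section** (control vs experimental at week 24): UAER 70 ± 51 vs 44 ± 27 mg; 24-h UP 3.25 ± 1.09 vs 2.50 ± 0.95 g; eGFR 33.4 ± 9.1 vs 40.5 ± 10.2. Allocation is 1:1, power about 90%, "a one-side level of significance of 0.05", dropout 20%. **Assumed:** a correlation ρ between baseline and week 24, which the article does not give, shown at 0.3, 0.5 and 0.7.

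**1. The plan's own figures.** With k = 1 the formula is n = (1.64 + 1.28)² × (s₁² + s₂²)/(μ₂ − μ₁)².
- Early: 8.526 × (2601 + 729)/676 = 42.0; 42/0.8 = 52.5, so 53.
- Middle: 8.526 × (1.188 + 0.903)/0.5625 = 31.7, so 32; 32/0.8 = 40.
- Advanced: 8.526 × (82.81 + 104.04)/50.41 = 31.6, so 32; 32/0.8 = 40.
- Total: 2 × (53 + 40 + 40) = 266.

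The stated sizes reproduce. The formula is that of an unadjusted comparison of two week-24 means, so it matches the planned t test.

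**2. Power of the unadjusted t test.** The pooled SD is √((s₁² + s₂²)/2), giving 40.8 mg, 1.02 g and 9.67 mL/min/1.73 m². The standardized effects d are 0.64, 0.73 and 0.73. Power is from the noncentral t distribution with noncentrality d√(n/2).

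| n per arm (early/middle/advanced) | One-sided 0.05 | Two-sided 0.05 |
|---|---|---|
| 42/32/32 (20% lost) | 89.5/89.6/89.6% | about 82% in each |
| 53/40/40 (all analysed, effect undiluted) | about 95% | about 90% |

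**3. Adding baseline.** The residual SD becomes SD × √(1 − ρ²), so the required n falls by the factor 1 − ρ². At 42/32/32 per arm:

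| Assumed ρ | 1 − ρ² | One-sided power | Two-sided power |
|---|---|---|---|
| 0 (unadjusted) | 1.00 | about 90% | about 82% |
| 0.3 | 0.91 | 92% | 86% |
| 0.5 | 0.75 | 96% | 91–92% |
| 0.7 | 0.51 | 99% | 98% |

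The three stages agree to within rounding. Two-sided power reaches 90% at these numbers only from ρ of about 0.45. Spending six further degrees of freedom on centre changes two-sided power by about 0.1 percentage point.

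**4. Chance imbalance.** The standard error of the baseline difference, in SD units, is √(2/n): 0.22 at n = 42 and 0.25 at n = 32. The central 90% range is ±1.645 times that, or ±0.36 and ±0.41 SD. Multiplied by ρ, this passes into the week-24 difference. At ρ = 0.5, and measured in week-24 SDs, that is 0.18 to 0.21 SD, against planned effects of 0.64 to 0.73 SD. For UAER it is 0.18 × 40.8 = about 7 mg against the planned 26 mg.

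**5. If change from baseline is what is tested.** The article does not say whether the week-24 value or the change is compared; the sample size uses week-24 values. With equal SDs at both times, a change score has variance factor 2(1 − ρ): 1.40, 1.00 and 0.60 at ρ = 0.3, 0.5 and 0.7. The adjusted factors of 0.91, 0.75 and 0.51 are smaller in every case.

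**6. Centre.** No between-centre variance is given, so the excess in the standard error cannot be computed.

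**The case against.** The strongest reply is that nothing here is wrong. An unadjusted comparison of randomized arms is valid, the sample size was computed for it, and it delivers the stated power at the stated one-sided level. That stands. A reader might infer that the plan throws away power the trial needs, pointing to the 82%. The documents do not support this. The 82% requires both a two-sided reading of the P < 0.05 rule, whose sidedness is not stated, and the loss of 20% of patients from the analysis. The article plans an intention-to-treat analysis with last observation carried forward. If all 53/40/40 are analysed with the effect undiluted, two-sided power is about 90%. Sidedness is a separate matter.

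It also stands that the size of the gain rests on an assumed correlation. At ρ = 0.3 the gain is small and does not bring two-sided power to 90% at the evaluable numbers.

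It would be too strong to say that the design factors are ignored. Stage is fully handled, because each stage is analysed separately. Centre and the repeated measurements, baseline included, do appear, though only in optional analyses. Omitting a stratification factor makes inference conservative, not invalid.

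Two further inferences should be resisted. The first is that the t test or the Mann-Whitney test will be chosen after seeing the data. The article gives no timing for the choice, a selection rule may sit in the unseen analysis plan, and the analysts are blinded. The second is that a log scale is required. Pilot UAER looks right-skewed, but the trial was planned on differences in means, and a log scale changes the quantity estimated. Nor does it bring the gain by itself: in 10,000 simulated lognormal trials matched to the pilot UAER (42 per arm, two-sided 0.05), power was 87.8% for the raw t test, 86.2% for the t test on logs and 84.4% for Mann-Whitney.

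What survives is that the article does commit to a primary test, and that this test leaves collected prognostic information unused.

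**Conclusion.** The point holds as a recommendation on efficiency, not as an error. The primary test omits a baseline measurement that is already collected and leaves a randomization stratum to an optional analysis. With the pilot effects and 42/32/32 evaluable per arm, baseline adjustment would lower the required sample size by 9%, 25% or 49% at ρ = 0.3, 0.5 or 0.7. It would also remove most of the influence of chance baseline differences on the estimate. These figures rest on the pilot means and SDs, on the assumed correlation, and on a roughly linear relation between baseline and week 24 with similar spread in both arms. The effect of omitting centre is in a known direction (a standard error that is too wide if centres differ), but its size is unknown.

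**What to change.** In the Statistical analysis section, name one primary analysis for each stage: a linear model of the week-24 value on arm, the baseline value of the same variable, and centre. Report the adjusted difference between arms with its 95% confidence interval. Set in advance a rule for pooling very small centres. Keep the t test and the Mann-Whitney test as sensitivity analyses.

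A log scale for UAER and 24-h UP may be considered. If it is adopted, the effect becomes a ratio of geometric means, and the choice must be fixed before unblinding.

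The cost is a change of wording. All variables are already collected, the sample size need not change, and the article reports that recruitment is under way, so the change can be made before any data are unblinded.

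### The supplementary repeated measures ANOVA tests a time effect and an any-visit interaction, and neither estimates the week-24 treatment effect on which each stage was sized

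*Protocol article*

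**What the plan says.** The Statistical analysis section describes the three primary outcomes (UAER in early, 24-h UP in middle and eGFR in advanced stage) as variables "which are all continuous variables with four measurements". For the main analysis it says that the independent-samples t "test or Mann-Whitney test will be used for comparison of the trial primary outcomes between the two groups". It then adds that "repeated measures analysis of variance will be attempted to further test the time effect and treatment cross-effect". It lists no factor levels, baseline covariate, week-24 contrast or sphericity correction for that model.

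The visits are fixed elsewhere. Study design has "Four visits will be scheduled for each patient: weeks 0 (baseline), 4, 12, and 24", and Data collection agrees: "The participants will be evaluated at baseline and weeks 4, 12, and 24". Sample size is tied to one time point: the number of patients that "would allow obtaining a significantly lower UAER in the experiment group after 24 weeks of treatment", with similar calculations for the other two stages.

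**The concern.** Only four visits exist and one precedes treatment, so four measurements must include baseline. A repeated measures ANOVA with a time factor over them then treats baseline as a response.

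The two effects named do not answer the question the trial was sized for. The time effect is the average change in both arms together, so it can be significant when treatment does nothing. The interaction asks whether the arms' profiles differ in any way over the four occasions. It does not say at which visit or in which direction, and it gives no week-24 estimate. A supportive result could therefore agree or disagree with the main comparison for reasons unrelated to week 24. The classical F test also assumes sphericity, which fails if correlation weakens as visits lie further apart.

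**Working it through.** **1. The plan's own sizing, from its pilot values.** n per arm = (1.64 + 1.28)² × (s₁² + s₂²) / (μ₂ − μ₁)², with (2.92)² = 8.5264.
- Early: 8.5264 × (51² + 27²) / 26² = 8.5264 × 3330 / 676 = 42.0; 42 / 0.8 = 52.5, so 53.
- Middle: 8.5264 × (1.09² + 0.95²) / 0.75² = 31.7, so 32; 32 / 0.8 = 40.
- Advanced: 8.5264 × (9.1² + 10.2²) / 7.1² = 31.6, so 32; 32 / 0.8 = 40.
- Total: 2 × (53 + 40 + 40) = 266.

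All figures reproduce, and all rest on the week-24 difference.

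**2. What the interaction responds to.** It has (2 − 1) × (4 − 1) = 3 df and depends on the sum of squared deviations of the four between-arm differences from their own mean. With δ the planned difference, at weeks 0, 4, 12 and 24:
- Week 4 only (0, δ, 0, 0): mean δ/4; sum = (9 + 1 + 1 + 1)/16 δ² = 0.75 δ².
- Full effect from week 4 on (0, δ, δ, δ): mean 3δ/4; sum = (9 + 1 + 1 + 1)/16 δ² = 0.75 δ².
- Linear build-up (0, δ/6, δ/2, δ): mean 0.4167δ; sum = (0.1736 + 0.0625 + 0.0069 + 0.3403) δ² = 0.583 δ².

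Under equal correlation, an effect that has vanished by week 12 counts as much as one that lasts to week 24, and more than one that builds up to the planned week-24 value.

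**3. Simulation.** Inputs from the plan: the pilot differences and pooled SDs. Early stage: 26 / √((51² + 27²)/2) = 26 / 40.8 = 0.637. Middle stage: 0.75 / 1.02 = 0.734. Completers are 42 per arm (early) and 32 (middle). Assumptions not in the documents: normal data, equal variances, two-sided 0.05, and a week-0 to week-24 correlation of 0.3 to 0.7, either equal between all visits or decaying with time.

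*Difference at week 4 only* (42 per arm; equal correlation 0.5, or decaying 0.3 to 0.7): the interaction is significant in 85–100% of trials; week-24 tests stay near 5%.

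*Linear build-up to the planned week-24 difference* (ranges cover both correlation patterns where both were run):

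| Correlation, stage | Interaction | Unadjusted week-24 t test | Baseline-adjusted week 24 |
|---|---|---|---|
| 0.5, early | 75–79% | 81–82% | 90–92% |
| 0.7, early | 94–96% | 82–84% | 98% |
| 0.3 decaying, middle | 64% | 83% | 86% |

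*Full effect from week 4 on:* the interaction has at least 85% power at correlation 0.5 or above. It can exceed the adjusted contrast (middle stage, decaying 0.5: 98% against 91%).

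With complete data, the week-24 contrast from a mixed model with unstructured covariance and baseline-by-visit terms is the baseline-adjusted comparison in the last column.

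**4. Sphericity.** Null rejection rate of the uncorrected interaction F test, 53 per arm:

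| Correlation (decaying) | Epsilon, weeks 0/4/12/24 | Error | Epsilon, even spacing | Error |
|---|---|---|---|---|
| 0.3 | 0.72 | 6.6% | 0.78 | 6.2% |
| 0.5 | 0.67 | 7.1% | 0.73 | 6.6% |
| 0.7 | 0.64 | 7.3% | 0.69 | 6.9% |

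Equal correlation gives 5.0% at any spacing. With 10% measurement noise added (epsilon about 0.8), the error is 5.8–6.7%. With the Greenhouse-Geisser correction it is about 4.3–5.1%.

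**The case against.** The strongest reply is that this analysis is secondary by the protocol's own wording: it comes after the t test or Mann-Whitney test, will only be attempted, and serves to test further. No decision rule hangs on it, and the main test can supply a week-24 difference. A profile test that asks another question is not in itself an error. With baseline included, the interaction validly tests whether change from baseline differs between arms. All of this stands and limits the weight of the point. It does not make the named effects informative about week 24.

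Four stronger readings are tempting, and the documents do not support them.
- That the protocol takes the time effect as evidence of treatment benefit. It says only that the effect will be tested.
- That a group main effect diluted by baseline will be reported. Averaging in the baseline zero would leave (0 + 1/6 + 1/2 + 1)/4 = 42% of the week-24 effect under linear build-up, but the section does not name that effect.
- That the interaction is always the weaker test. At correlation 0.7 it beats the planned unadjusted t test, and with immediate onset it can beat the adjusted contrast too.
- That uneven visits make the test liberal. Decaying correlation does most of that, and uneven spacing adds about 0.4 to 0.5 percentage points. The protocol neither names nor excludes a correction, and an analysis plan could supply one.

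The inclusion of baseline is also an inference. The Fig. 2 legend can be read as giving 24-h UP only at weeks 0, 12 and 24. With three occasions the interaction has 2 df and the argument is unchanged.

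**Conclusion.** The point holds for the supplementary longitudinal analysis and no further. A reader might infer that the trial's primary test is biased or liberal; the t test or Mann-Whitney comparison is untouched by it.

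The firm part needs no assumed correlation: the time effect pools the arms, the interaction is an any-visit test, and neither estimates the week-24 effect behind the 266 patients. The power loss against a baseline-adjusted week-24 contrast is conditional on gradual onset. It is roughly 11 to 17 percentage points at correlation 0.5 (75–79% against 90–92%) and 2 to 4 at 0.7 (94–96% against 98%), early stage, 42 per arm, normal data. The type I error of about 6–7% is conditional on decaying correlation and no correction. This is a worthwhile, inexpensive improvement rather than a threat to the main conclusion.

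**What to change.** In the Statistical analysis section, replace the repeated measures ANOVA with a mixed model for repeated measures, fitted separately in each stage (SPSS MIXED):
- responses: the post-baseline visits only, as observed rather than carried forward;
- terms: treatment, visit, treatment-by-visit, baseline and baseline-by-visit;
- covariance: unstructured (with three visits, 3 × 4 / 2 = 6 parameters);
- result: the week-24 treatment contrast with its 95% CI as the supportive estimate, and the week-4 and week-12 contrasts as description.

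The section should also say that the pooled time effect is not read as a treatment effect, and that the last-observation-carried-forward rule does not apply to this model.

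The cost is a few sentences and another procedure in the software already named, with no new data. The single any-visit test is given up, and the model relies on a missing-at-random assumption in place of the carried-forward rule.
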